**Figure 1 F1:**
[figure not shown]
**Flow of participants through the trial**.

### Participants

Participants will be consenting people aged over 18 years with a DSM-IV diagnosis of primary PTSD. The study sample will consist of patients from St John of God Healthcare's Richmond Hospital, located in Sydney, Australia. To be eligible for study inclusion, participants must be considered medically fit to participate in an exercise program by the consulting medical officer. All participants must be cognitively able to provide consent.

People will be ineligible to participate in the trial if they are medically unfit to participate, are pregnant or planning pregnancy within the next year and if they are diagnosed with complex PTSD with trauma occurring in childhood only.

### Ethical considerations

Full ethical approval for this study has been obtained from St John of God Healthcares Ethical Committee (REF: 412). Written informed consent from all participants will be obtained prior to the baseline assessment. The research team will be advised by nursing and/or medical staff as to whether potential participants are cognitively able to provide consent.

### Randomisation

Upon admission to the hospital as either an in-patient or out-patient, a routine physical assessment will be conducted by a consulting medical officer to assess trial eligibility based on physical limitations. This initial assessment will also be used to confirm that the potential participant meets the DSM-IV diagnosis of PTSD. Eligible subjects will then be invited to participate in the trial by the research team. Posters, flyers and other marketing material will be distributed around the facility to promote awareness of the trial. Outpatients eligible to participate will be informed of the study through hospital staff at various times throughout their contact with the hospital.

Once consent has been obtained, the baseline assessment will be conducted and participants will then be randomised to either the exercise intervention or control group. Allocation to groups will be undertaken by a staff member not involved in recruitment (to ensure allocation concealment) using a block randomisation sequence generated using random numbers in Excel and including randomly varying block sizes. Participants and intervention staff are unable to be blinded to group allocation, but health and exercise professionals assessing all outcome measures will be blinded to group allocation.

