## Methods/design

### Design

An assessor-blinded RCT will be conducted. A total of 40 participants in each group (n = 80) will be recruited. The study will have 80% power to detect as significant at the 5% level a 5 point between group difference on the PCL-C (SD = 9.4) [13] allowing 15% dropouts. The study protocol has been designed and will be reported, with reference to the CONSORT Statement [14]. Figure 1 gives an overview of the study design.

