#### Medication Usage

Pro re nata (PRN) medication usage specifically sleeping and as required psychotropic medication will be measured using a weekly self-report diary, and patient notes whilst admitted as an inpatient.

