### Statistical analysis

Regression models will be used to assess the effect of group allocation on the primary and secondary outcome measures after adjusting for baseline values. An intention-to-treat approach will be used for primary analyses. A secondary per-protocol analysis will be conducted excluding people who do not comply with the intervention, defined as performing less than 30% of the recommended exercise sessions. A further secondary analysis will assess whether there is an interaction between baseline physical activity levels and group allocation. Analyses will be conducted using the SPSS and Stata software packages.

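### In-patients and out-patients share one allocation sequence, and setting is not in the model: valid, but setting is a cheap covariate left unused

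*Protocol article*

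**What the plan says.** The Randomisation section of the protocol article takes in patients "Upon admission to the hospital as either an in-patient or out-patient". After consent, "the baseline assessment will be conducted and participants will then be randomised to either the exercise intervention or control group". Allocation is made by a staff member outside recruitment, "using a block randomisation sequence generated using random numbers in Excel and including randomly varying block sizes". The section describes a single sequence and names no stratification factor.

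The Statistical analysis section gives the model: "Regression models will be used to assess the effect of group allocation on the primary and secondary outcome measures after adjusting for baseline values". The one other use of a baseline factor is an interaction: "A further secondary analysis will assess whether there is an interaction between baseline physical activity levels and group allocation". Setting is not mentioned there.

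The Design section gives the size: "A total of 40 participants in each group (n = 80) will be recruited", with a target difference of 5 points on the PCL-C, SD 9.4 and 15% dropout.

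The Medication Usage section is the one outcome description that refers to setting: PRN use is "measured using a weekly self-report diary, and patient notes whilst admitted as an inpatient".

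**The concern.** Setting is a two-level factor, known for every participant before allocation and recorded at no cost. If it predicts the 12-week PCL-C score after baseline PCL-C is accounted for, leaving it out of both the list and the model has two costs:

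- With 40 per arm, the arms can differ noticeably in their in-patient share by chance, and the estimate moves with that difference.
- The variation between settings stays in the residual and widens the confidence interval.

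Whether setting does predict outcome is an inference. The article suggests only that the two routes into the trial differ: in-patients are approached around admission, and out-patients at differing points in their care. The PCL-C covers the past month, so the baseline score of someone just admitted may largely describe the time before admission and need not carry all the information in setting. None of this is quantified in the article.

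Prespecification has a further benefit. If an imbalance appears at the end, there is no argument about whether to adjust for it.

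**Working it through.** **Inputs from the article:** 80 randomised, 40 per arm; target 5 points; SD 9.4; 15% dropout, so 40 × 0.85 = 34 per arm analysed; 80% power at the 5% level (two-sided assumed, since sidedness is not stated).

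**Inputs assumed, because the article gives neither:** in-patient share p (0.2, 0.3, 0.5), and the PCL-C difference D between settings at 12 weeks given baseline (2, 5, 8 points).

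**Step 1. The plan's own figure.** For an unadjusted comparison of two means, n = 2 × [9.4 × (1.960 + 0.842) / 5]² = 55.5, so 56 per arm, and 56 / 0.85 gives 66 per arm after dropout. Forty per arm is not reproduced this way. With 34 analysed per arm, power is 59%. An ANCOVA reaches 80% with 34 per arm if the correlation between baseline and 12-week scores is r = √(1 − 34/55.48) = 0.62, a value the article does not state. That is a separate matter. Here it only supplies two ends of a range, r = 0 and r = 0.62:

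- r = 0: SE = 9.4 × √(2/34) = 2.28 points.
- r = 0.62: residual SD s = 9.4 × √(1 − 0.62²) = 7.38, and SE = 7.38 × √(2/34) = 1.79 points.

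**Step 2. Chance imbalance.** Given K = 80p in-patients split 40/40 without regard to setting, the number in one arm is hypergeometric.

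| In-patient share p | SD of difference in share | P(≥ 10 points, 4 or more people) | P(≥ 15 points, 6 or more) | P(≥ 20 points, 8 or more) |
|---|---|---|---|---|
| 0.2 | 9.0 points | 40% | 16% | 5% |
| 0.3 | 10.3 points | 46% | 22% | 9% |
| 0.5 | 11.3 points | 50% | 26% | 12% |

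**Step 3. Shift in the estimate.** Shift = difference in share × D. At a 20-point imbalance this is 0.20 × 2 = 0.4, 0.20 × 5 = 1.0 or 0.20 × 8 = 1.6 points. For D = 2 to 5 that is between 0.4/2.28 = 0.18 and 1.0/1.79 = 0.56 of a standard error. A typical imbalance matters less: one SD at p = 0.5 with D = 5 gives 0.113 × 5, about 0.6 points.

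**Step 4. Precision gained by adjusting.** The share of residual variance explained by setting is p(1 − p)D²/s². For p = 0.5, D = 5 and r = 0 it is 0.25 × 25 / 88.36 = 7.1%; for r = 0.62 it is 0.25 × 25 / 54.4 = 11.5%. Power with 34 per arm, for p from 0.3 to 0.5:

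| D (points) | r = 0: without → with setting | r = 0.62: without → with setting |
|---|---|---|
| 2 | 59.2% → 59.6–59.7% | 79.8% → 80.4–80.5% |
| 5 | 59.2% → 61.8–62.4% | 79.8% → 83.7–84.4% |
| 8 | 59.2% → 66.3–67.9% | 79.8% → 89.6–91.4% |

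The gain is therefore 0.4 to 4.6 percentage points for D of 2 to 5. The last row shows the scale only: a setting gap of 8 points, given baseline, would exceed the 5-point treatment effect the trial is built to detect.

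**The case against.** The strongest reply is that nothing here is wrong. Blocked, concealed allocation without strata gives an estimate that is unbiased over randomisations and keeps the type I error, and the ordinary standard error already allows for chance imbalance in setting. That stands. A reader might infer that the treatment comparison is biased or invalid; the design does not support that.

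Second, the article does not say that setting is prognostic. This also stands. A reader might further infer that in-patients are more acutely ill, are treated more intensively, recover faster after admission or have better gym access. The article states none of these. The Control Group section describes the hospital exercise programme for patients generally and says in-patients' self-initiated use is usually limited; it does not compare access by setting. Setting at entry may also be a blurred marker, because the article speaks of admission for both groups.

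Third, a reader might infer that adjusting for setting would cure unequal recording of PRN medication. It would not. The diary applies to everyone, and patient notes are an added source only during an in-patient stay. The difference follows admission status during the 12 weeks, not setting at randomisation.

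Fourth, further covariates might be listed in an analysis plan that is not shown, and the model statement does not say that baseline values are the only covariates. This has some force for the model. It has less for the list: stratification is a property of the allocation sequence, which the article describes in some detail as a single sequence, and a later plan cannot stratify it retrospectively.

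**Conclusion.** The point holds as a modest improvement to a valid design. Setting is known before allocation, yet the described sequence and model do not use it. Under an assumed in-patient share of 20% to 50%, an imbalance of 20 percentage points or more has a 5% to 12% chance. With an assumed setting gap of 2 to 5 points given baseline, such an imbalance moves the estimate by 0.4 to 1.0 points, which is well within one standard error, and adjustment gains from under half a percentage point to about 4.6 points of power. If baseline PCL-C already carries most of the difference between settings, the benefit is close to nil. Severity is low, and the case for acting rests on the very small cost.

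**What to change.** Name setting at randomisation (in-patient or out-patient, as recorded at that moment) as a fixed covariate alongside the baseline value in the primary and secondary regressions. If allocation has not begun, also generate the varying-block sequence separately for each setting, giving two lists under the same concealment. If allocation has begun, leave the list alone and add only the covariate, before outcome data are examined by group.

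The cost is one degree of freedom per model and a second list. No extra data or participants are needed. The covariate should not be presented as a remedy for the differing sources of PRN medication data.

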### Intervention

The exercise intervention will comprise a minimum of three exercise sessions per week, with one session completed at the hospital under supervision of an exercise physiologist and the other two completed without supervision. All required exercise equipment will be supplied to participants for the duration of the study. The exercise protocol consists of a series of progressive compound exercises using exercise bands and body weight for resistance. Participants will perform 3 sets of 10 repetitions of each exercise. A warm-up set that is one intensity level below the 'overload sets' will also be included. A rest period of between 10 and 30 seconds will be allowed between sets. Once exercise technique is considered competent by the exercise physiologist or research nurse, participants will be advised to perform all exercises in a circuit like manner, adding a cardio-respiratory component to the exercise sessions. Exercises are outlined in Table 1.

**Table 1 T1:** REAP Exercise Chart showing exercises and progression of intensity for each exercise

Exercise	Level 1	Level 2	Level 3	Level 4	Level 5	Level 6	Level 7
**^1^Chest press**	EB* 'light'	EB 'medium'	EB 'heavy'	EB 'extra heavy'	Incline push-ups	Knee push ups	Push ups

**^1^Row**	EB 'light'	EB 'medium'	EB 'heavy'	EB 'extra heavy'			

**^1^Squats**	Seated leg press (single leg)	Sit-to-stand	squats	EB 'light'	EB 'medium'	EB 'heavy'	EB 'extra heavy'

**^1^Core/mid section**	Wall hold	4-point kneeling	4-point kneeling with resistance	Prone hold			

**^2^Lat/overhead pull-down**	EB 'light'	EB 'medium'	EB 'heavy'	EB 'extra heavy'			

**^2^Upright row**	EB 'light'	EB 'medium'	EB 'heavy'	EB 'extra heavy'			

**^3^Bicep curl**	EB 'light'	EB 'medium'	EB 'heavy'	EB 'extra heavy'			

**^3^Triceps extension**	EB 'light'	EB 'medium'	EB 'heavy'	EB 'extra heavy'	Chair dips		

**^3^Leg extensions**	Body weight (single leg)	EB 'light'	EB 'medium'	EB 'heavy'	EB 'extra heavy'		

*EB exercise band

^1 ^Indicates 'Key Exercise'

^2 ^Indicates 'Secondary Exercise'

^3 ^Indicates 'Additional Exercise'

Each exercise session with the exercise physiologist will last for approximately 30 minutes. Sessions will be predominantly one-on-one, however during the later stages of the intervention it is expected that up to three participants could be present in a single exercise session.

During the initial exercise session, results from the physical assessment, International Physical Activity Questionnaire (IPAQ) [15] and the Borg Rating of Perceived Exertion Scale (RPE) [16] will be used to assign the initial program intensity from the Randomised Exercise Augmentation for PTSD (REAP) exercise table. It is expected that most of the cohort will be sedentary at the time of recruitment so exercises will be introduced in a staged manner in order to maximise adherence and technique acquisition. The REAP exercises have been segmented into 'Key', 'Secondary' and 'Additional' exercises indicating the order in which they will be introduced into the program. Individual limitations such as arthritic conditions, skill and coordination will also be considered when prescribing the exercises. For example if a participant is able to perform ten repetitions of the Level 1 chest press with an RPE below 12/20 (indicating light exertion), then the Level 2 progression will be attempted. Discretion will be used when applying the RPE scale. The weekly exercise sessions with the exercise physiologist/research nurse will be used to address any issues that participants may have with exercise technique, exercise progressions and adherence.

In addition to the resistance exercise program, a walking program will be included. Participants randomised to the intervention group will be provided with an Omron HJ109 pedometer in order to quantify daily step count. Participants will be asked to record their daily step count on the exercise diaries provided and the results of which will be used to assist with goal setting and motivation. Participants will be encouraged to aim for an ultimate daily target of 10,000 steps per day [17] which can be broken down into a series of short and incidental walks, in order to maximise feasibility and adherence.

Participants in the exercise group will also receive usual treatment for PTSD involving a combination of psychotherapy, pharmaceutical interventions and group therapy facilitated by psychologists. Voluntary programs including yoga, art therapy and use of the hospital gymnasium will also be available.

### Motivational Tools

Defined behaviour change techniques (BCT's) such as barrier identification, general encouragement, setting of graded tasks, instruction, specific goal setting, self-monitoring and feedback will be incorporated into the intervention program to enhance engagement and uptake of the intervention [18]. Exercise diaries and motivational interviewing will be a major component of the BCT's used. As recommended by the National Institute for Health and Clinical Excellence (NICE) 2007 guidelines on behaviour change at population, community and individual levels [19], the exercise physiologist and research nurse will use a combination of strategies to increase physical activity participation. Structured strategies to overcome common barriers to exercise will also be used. These strategies can be found in Table 2  
[20]. Exercise diaries in the form of a printed spread-sheet will be provided and participants will be encouraged to record the date, time, number of sets and repetitions performed, and amount of walking done per day (measured with a pedometer). The diaries will also be used to guide progression of the intensity of individual exercise programs.

**Table 2 T2:** Methods of improving behaviour change and overcoming barriers to exercise participation [19,20]

Ensure participants have an understanding of the short, medium and longer-term consequences of their health-related behaviours, for themselves and others
Assist participants to plan their behaviour changes in terms of easy steps over time

Recognise how social contexts and relationships may affect behaviour, and identify and plan for situations that might undermine changes being made

Plan explicit 'if-then' coping strategies to prevent relapse

Assist participants to make a personal commitment to adopt health-enhancing behaviours by setting (and recording) goals to undertake clearly defined behaviours, in particular contexts, over a specified time

Share their behaviour change goals with others

Encourage short bouts of exercise for participants with a 'lack of time'

Encourage group exercise sessions for participants with low motivation

Encourage moderate level activities if physical limitations are present

### Control Group

The control group will receive usual care, which will involve a combination of psychotherapy, pharmaceutical interventions and group therapy facilitated by psychologists. Access to these treatments by both the control and intervention groups will be recorded through use of the hospital database and patient files. Voluntary programs including yoga, art therapy and use of the hospital gymnasium will also be available. Access to the hospital exercise program is determined by the consulting medical physicians and the exercise physiologist. The control group will be asked to limit their participation in any exercise program that they do not usually undertake, however access to the usual hospital exercise program will not be restricted for the purpose of this research. The hospital exercise program involves two, one hour sessions per week in which patients have access to the gymnasium and an exercise physiologist. Equipment available includes treadmills, exercise bands and a limited number of machine weights. Self-initiated use of the hospital exercise program by in-patients with PTSD is usually limited, and it is not expected that this would have significant ramifications for the research. Participants randomised to the control group who wish to exercise will be permitted under the usual policy of the hospital, and participation will be monitored and recorded.

### Outcomes

#### Data Collection

Data will be collected from clinician interviews, self-report questionnaires, exercise, medication use and sleep diaries, and physical assessments. Health or exercise professionals collecting data will be blinded to group allocation. Physical assessments will be carried out at baseline, and following the 12 week intervention. All tests will be conducted in an examination room at the hospital. Assessments will take approximately 30 minutes to administer. All assessments will be carried out by an assessor blinded to group allocation.

### Outcome measures

#### Post Traumatic Stress Disorder symptoms

The primary aim of this study is to examine the effects of individualised, structured exercise on PTSD symptoms. This will be measured using the PTSD Checklist-Civilian [21], a self-report questionnaire comprising 17 items relating to the main symptoms of PTSD. Participants are asked to indicate how much they have been bothered by a particular symptom over the past month using a 5-point (1-5) scale.

#### Depression and Anxiety

The Depression Anxiety and Stress Scale (DASS) [22] will be used to assess the effects of the program on depressive and anxiety symptoms. The DASS is a 42-item self report instrument that measures the related negative emotional states of depression, anxiety and tension/stress.

#### Mobility, Fitness and Strength

Assessments of mobility will include tests of standing balance [23] (tandem, semi-tandem and single-leg stance time), the ability to rise from a chair, and the 6-minute walk test [24]. Upper limb strength will be assessed using a hand grip dynamometer with a single assessment to be carried out on each upper limb [25]. Knee extension strength will be assessed with a spring gauge attached to the participant's leg using a webbing strap with a Velcro fastener. The participant will extend their knee pulling against the strap with maximal force for 2-3 seconds with each leg to be tested 3 times and the best score recorded [26].

#### Body Composition

Measurements will include resting heart rate, blood pressure, weight, height, body mass index, body fat percentage (to be obtained using a Tanita bio-impedance scale), waist circumference (defined as the point midway between the iliac crest and costal margin) and hip circumference (defined as the widest part of the gluteal region).

#### Physical Activity Levels

Physical activity participation will be measured the short version of the IPAQ [15]. The IPAQ (short form) includes 7 questions relating to the amount of time spent per week engaging in vigorous and moderate physical activity, walking and sedentary activities.

#### Sleep Patterns

Sleep habits and patterns including amount of sleep hours per night and barriers to sleep will be monitored through the Pittsburgh Sleep Quality Index [27] and the Pittsburgh Sleep Quality Index Addendum for PTSD [28]. Both instruments are self-report questionnaires that assess sleep quality in the past month.

#### Medication Usage

Pro re nata (PRN) medication usage specifically sleeping and as required psychotropic medication will be measured using a weekly self-report diary, and patient notes whilst admitted as an inpatient.

### Statistical analysis

Regression models will be used to assess the effect of group allocation on the primary and secondary outcome measures after adjusting for baseline values. An intention-to-treat approach will be used for primary analyses. A secondary per-protocol analysis will be conducted excluding people who do not comply with the intervention, defined as performing less than 30% of the recommended exercise sessions. A further secondary analysis will assess whether there is an interaction between baseline physical activity levels and group allocation. Analyses will be conducted using the SPSS and Stata software packages.

